### Blinding and randomisation

Randomisation will occur within each cohort once consenting schools have completed baseline assessments. Schools will be matched as closely as possible based on the following characteristics in this order: (1) school type (ie, mainstream school support class/SSP), (2) school sector (ie, government/Catholic/independent), (3) geographic location (ie, region, rural/urban, coastal/inland) and (4) student population educational advantage (ie, using the Index of Community Socio-Educational Advantage).^30^ Matched schools will be randomised to the intervention or waitlist control group using a random number producing algorithm by an independent statistical analysis service – Clinical Research Design, Information Technology and Statistical Support run by the Hunter Medical Research Institute. One school from each pair will be allocated to the B2La condition and the other to the waitlist control condition. Schools randomised to the intervention group will deliver the B2La programme during the study period, whereas schools allocated to the waitlist control group will continue with usual school practice (ie, normal curricular lessons) for the duration of the study period and will receive the intervention the following year. We decided to use a waitlist control design, rather than an attention-matched placebo because: (1) our research team will have minimal contact with students, and (2) our findings will have greater external validity, as participants in the control group will receive ‘usual practice’.

### Patient and public involvement

Following the B2L cluster RCT, our research team was asked to adapt the intervention for students with disability. We subsequently conducted a feasibility study in one secondary school in Newcastle (n=16 students).^24^ Participating students and teachers were invited to provide feedback on the intervention and suggestions for further improvement. This feedback was then used to refine intervention components (eg, exercise sessions) and develop implementation strategies (eg, professional learning for teachers). We then partnered with the NSW Department of Education and Special Olympics Australia to create B2La. We conducted further testing with teachers and students with disability before progressing to this trial.

### Intervention

#### Intervention delivery

The B2La intervention will be delivered in four phases:

Laying the foundation (weeks 1–4).Developing a routine (weeks 5–9).Maintaining student interest (weeks 10–16).Moving towards independence (week 17 onwards).

In phases 1–3 (16 weeks), teachers will facilitate the delivery of at least two HIIT sessions/week during lesson time. Phase 1 will start with a 4 week block to familiarise students with the B2La session structure and support resources and to develop the foundational exercise skills that are used within the HIIT sessions utilising the B2La technique cards (figure 1). During this phase, students will participate in two HIIT workouts: indoor HIIT and power HIIT (as shown in figure 2). These basic HIIT workouts do not require additional sport equipment or partner interaction. This will allow students to develop their movement skill competency.

**Figure 1 F1:**
[figure not shown]
Example of B2La HIIT technique card. This figure was created by the lead investigator.

**Figure 2 F2:**
[figure not shown]
Examples of B2La HIITsession cards. This figure was created by the lead investigator.

In phases 2 and 3 (weeks 5–16), the number of foundational exercises used within the HIIT sessions will increase as students become more confident with the exercises and session routine. During this phase, there will be an increase in the work interval within the HIIT sessions. Students will also be introduced to novel HIIT-themed workouts, including: soccer HIIT and basketball HIIT (phase 2) and judo HIIT, cricket HIIT and custom HIIT (phase 3). During phases 2 and 3, teachers will be encouraged to increase the amount of autonomy provided to students (eg, choice of B2La session). In phase 4 (week 17 onwards), students will be encouraged to engage in physical activity sessions of interest outside of school (eg, at home, the park), but teachers may continue to facilitate B2La sessions during lessons if they choose. Students will have their own B2La goal setting activity booklet.

#### Intervention components

The B2La intervention includes the following components: student information seminar, school-based HIIT sessions, smartphone application (app), goal setting activity booklet and parental support videos.

##### Student information seminar

This seminar will be delivered by teachers and provide students with an overview of B2La. The seminar will focus on the barriers and benefits of physical activity for adolescents with disability^4^, as well as evidence-based behaviour change techniques (eg, self-monitoring, self-assessment, and goal setting). Teachers will be provided with a PowerPoint presentation template with embedded videos developed specifically for this project.

##### School-based HIIT sessions

Sessions will be delivered during scheduled ‘Learning Support Lessons’, a time period when adolescents with disability are working separately to those without disability (for those attending mainstream schools). Students with special needs in Australian mainstream secondary schools typically attend three, 2-hour support lessons per week. Teachers will be asked to facilitate the delivery of at least two exercise sessions per week in phases 1–3. Adapted from the original B2L intervention, teachers/participants will be able to select from predesigned themed HIIT workouts that include a combination of foundational resistance exercises (ie, push up, squat, front support, and lunge) and aerobic exercises (ie, shuttle run and high knees running on the spot). The sessions last 10–20 min including an appropriate warm-up. Due to the wide range of abilities expected from the participants, teachers will be encouraged to adapt the specific types of exercises and task complexity for each student. The task complexity and variations within the HIIT sessions will progressively increase over the study period. To monitor exercise intensity, students will be equipped with heart rate sensors (Polar Verity Sense) that will pair with a purpose-built iPad application (hereafter ‘app’) using Bluetooth connectivity. Students will be encouraged to reach a target intensity of ≥80% of age-predicted heart rate maximum during the work intervals. As demonstrated in our feasibility study, this heart rate target is achievable for students with disability.^24^

##### Smartphone app

Teachers and students will be provided with access to a bespoke smartphone app available via both Android and iOS operating systems. The app includes: (1) a teacher version that allows whole-class heart rate monitoring during ‘class’ sessions, (2) descriptions and depictions of exercise sessions, (3) options for ‘solo’ or ‘group’ sessions, (4) timer, audible prompts and display of heart rate using Bluetooth-synced heart rate monitors during HIIT sessions, and (5) personalised reports outlining heart rate. For students who do not own a smartphone, access to the B2L app will be provided to parents. During the professional development workshop, teachers will be encouraged to deliver school-based sessions using the teacher version that allows whole-class heart rate monitoring. Students will be encouraged to use the app during activity sessions outside of the school setting.

##### Goal setting activity booklet

Students will be provided with a goal setting activity booklet and encouraged to set physical activity and fitness goals over the study period.

##### Parent support videos

Parents will receive two e-newsletters containing links to video overviews of B2La, the benefits and barriers of physical activity for individuals with disability and strategies to support their children’s participation in physical activity outside of school. The e-newsletters will be delivered to parents in phases 1 and 2 of the intervention.

#### Intervention conceptual model and theoretical frameworks

B2La was guided by the conceptual model proposed by Lubans and colleagues,^31^ which includes four complementary tenets that are fundamental to the successful scale-up of adolescent HIIT interventions.

##### Opportunity

The B2La sessions will be delivered during scheduled ‘Specialist Support Classes’ (students typically attend 3×2-hour support lessons/week). These classes cater for students with moderate-to-high learning and support needs, including students with intellectual disability, mental health issues, autism, physical disability, sensory impairment and behaviour disorders. Based on our formative research with teachers and the NSW Department of Education, ‘Specialist Support Classes’ represent an ideal ‘new’ opportunity^32^ for the delivery of B2La.

##### Design

The school-based exercise sessions will provide participants with opportunities to collaboratively develop their exercise competence, confidence, and knowledge. Participants will also be provided with opportunities to design and run their own HIIT sessions. The study information seminar will focus on the benefits and barriers of physical activity for individuals with disability^4^ as well as evidence-based behaviour change techniques.

##### Delivery

B2La has been guided by Self-Determination Theory (SDT) to enhance students’ autonomous motivation for physical activity.^33^ Aligned with SDT, teachers will be provided with training and support to deliver the B2La sessions using the ‘Supportive, Active, Autonomous, Fair and Enjoyable’ (SAAFE) principles.^34^ Participants’ need for autonomy will be satisfied by providing opportunities for choice within sessions (eg, type of activity, music playing and training partner). Competence will be satisfied using positive and skill-specific feedback from teachers, with a focus on effort over performance (via heart rate feedback). Schools will also be provided with resources designed to support the accessibility, engagement, and development of exercise skills (eg, technique cards, B2L app). Teachers will use a variety of strategies to enhance group cohesion and satisfy students’ needs for relatedness during HIIT sessions (ie, encouraging supportive behaviour among students such as ‘high fives’ and facilitating partner work).^35^

##### Support

The implementation of B2La will be supported by the Consolidated Framework for Implementation Research (CFIR).^36^ Strategies used to facilitate the implementation of the B2La intervention will cover the five CFIR domains: intervention characteristics, outer setting (educational authorities), inner setting (schools), characteristics of individuals (teachers) and the implementation process (see table 1).

**Table 1 T1:** Strategies used to facilitate implementation in the Burn 2 Learn (B2L) adapted (B2La) intervention

Domains	Constructs	Strategies
B2La intervention characteristics	Evidence strength and quality	Findings from B2L cluster RCT and B2La feasibility study used in promotional and training materials.
	Adaptability	Flexible intervention delivery model (ie, during class-time or breaks, or between classes) requiring minimal access to facilities (ie, can be done in the classroom) and equipment (ie, body weight exercises).
	Complexity	Time-efficient intervention requiring only two or three 15–20 min sessions per week.
	Design quality and packaging	B2La programme resources developed by a professional graphic designer. Multimedia designed using evidence-based principles for learning.
Outer setting (educational authorities)	Partnerships and investment	Partnership with the NSW Department of Education and Special Olympics Australia.
	External policy and incentives	Professional learning accreditation with state-based educational standards authority.
Inner setting (schools)	School culture	Teachers will be encouraged to give a presentation to school staff focused on the benefits of activity for students’ mental health and academic outcomes.
	Leadership engagement	Teachers and external change agents will meet with the school principal to ensure commitment.
	Equipment	Schools will be provided with an equipment pack (~$A2000).
	Relative priority	Promoted to schools as strategy to improve students’ cognitive function and mental health.
Characteristics of individuals (teachers)	Self-efficacy, knowledge and beliefs (teacher)	Full day professional development workshop provided for teachers. Online version of workshop available.
	Perceived barriers (students)	Designed to be time-efficient, and motivating for students, through the SAAFE teaching principles.
Implementaton process	Planning for implementation	Teachers required to complete an action plan to support B2La implementation in their school.
	Champions	Recruitment of two school champions at each intervention school.
	External support agents	Schools will be allocated external change agent, who will visit twice for planning and evaluation.
	Evaluation and feedback	External change agents will conduct session observations and provide feedback to teachers.

SAAFE, Supportive, Active, Autonomous, Fair and Enjoyable.

Teachers recruited as school champions will attend a full day professional learning workshop led by members of the research team. The workshop will provide teachers with the training and resources needed to facilitate school-based HIIT sessions. The workshop will involve a combination of theoretical (ie, programme rationale, benefits of HIIT and school implementation plan) and practical (eg, participation in a B2La HIIT session, peer assessment of exercise technique and overview of how to use programme resources) activities.

### Measures and data collection

Trained research assistants, blinded to group allocation at all time-points, will conduct assessments for the primary outcome. Questionnaires will be completed with the assistance of research assistants using electronic tablets. Physical assessments will be conducted in a sensitive manner by a research assistant of the same sex where possible. Standard demographic information (eg, age, sex, ethnicity, country of birth, residential postcode and parent/caregivers’ education level) will be collected at baseline. All measurements will be conducted at baseline, 6 months postbaseline (primary endpoint) and 9 months postbaseline. The only exception will be students’ on-task behaviour, which will be assessed at baseline and midintervention (3 months postbaseline), and cognitive function, which will be assessed at baseline and 6 months only. Of note, due to physical and intellectual limitations, not all participants will be able to complete all measures, and modifications will be made, as necessary.

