**Trial registration number:**

Australian New Zealand Clinical Trials Registry Number: ACTRN12621000884808.

Strengths and limitations of this studyOur cluster randomised controlled trial will be adequately powered to detect meaningful changes in the primary outcome functional capacity.Informed by our pilot work, we have tailored the intervention and assessment processes to increase accessibility for the unique study population.The Burn 2 Learn adapted intervention has been designed in consultation with adolescents with disability, and key stakeholders (ie, NSW Department of Education and Special Olympics Australia).Having a unique study population with physical and/or intellectual limitations, not all participants will be able to complete all measures.It might not be possible to blind assessors for all outcomes, as group allocation is often revealed by research participants and teachers during post-test assessments in school-based trials.

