#### Primary outcome

##### Functional capacity

Consistent with previous physical activity interventions targeting youth with disability,^37^ our primary outcome is functional capacity, assessed using the 6MWT,^38^ which has good reliability in adolescents with disability (ICC=0.82).^27^ The 6 min push test will be used for students who self-propel a wheelchair.^39^ Students will be instructed to cover as much distance as possible in 6 min, and the distance (in metres) covered will be documented.

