##### Physical literacy

Autonomous motivation for physical activity will be assessed using identified and intrinsic subscales from the ‘Behavioural Regulations in Exercise Questionnaire-2’.^46^ Confidence will be assessed using the validated six-item High-Intensity Interval Training Self-efficacy Questionnaire.^47^ Competence will be assessed using video analysis of a selection of skills from the Resistance Training Skills Battery (ie, push-ups, lunge, squat and front support chest touch), which has been validated among typically developing adolescents^48^ and among children with varying degrees of motor skill proficiency.^49^

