## Discussion

B2La has been designed to provide older adolescents with disability an opportunity to be active at school but also focuses on developing their physical literacy (ie, physical competence, confidence, knowledge, and motivation) to engage in vigorous physical activity. Importantly, our research team will provide teachers with training and support to ensure that the programme is delivered in an engaging manner that supports students’ autonomous motivation to be active across the lifespan. Most HIIT studies have been delivered by researchers in controlled settings to establish efficacy, with little consideration of how they will work in the ‘real world’.^31^ By comparison, B2La was designed with scale-up in mind using the Consolidated Framework for Implementation Research to support implementation and sustainability. This may help to reduce the ‘voltage drop’ that typically occurs as interventions progress from efficacy to effectiveness to dissemination.^29 56–58^

The strengths of our study include the cluster RCT design. We also consider our intervention design to be a strength, as it was developed in consultation with adolescents with disability and key stakeholders (ie, NSW Department of Education and Special Olympics Australia). Our comprehensive assessment of physical, mental, and cognitive health is an additional study strength. However, there are potential limitations that should be noted. First, COVID-19 is still a major problem in Australian schools, resulting in high levels of teacher and student absenteeism. This is likely to affect recruitment, data collection and intervention implementation. Second, having a unique study population with physical and/or intellectual limitations, not all participants will be able to complete all measures. Finally, it might not be possible to retain the blinding of all research assistants at post-test assessments.

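### Assessor blinding is stated without qualification but only for the primary outcome, is elsewhere acknowledged to be at risk at post-test, and does not extend to video-rated exercise competence, where masking is feasible

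*Protocol article*

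**What the plan says.** **Scope of blinding.** The Measures and data collection section states: "Trained research assistants, blinded to group allocation at all time-points, will conduct assessments for the primary outcome". This is the only commitment to assessor blinding in the article. The section headed Blinding and randomisation describes matching and allocation but adds nothing on who is blinded. Statistical analyses commits to a blinded analysis, which is a separate safeguard.

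**Acknowledged risk.** The strengths-and-limitations box says "It might not be possible to blind assessors for all outcomes" and gives the reason: "group allocation is often revealed by research participants and teachers during post-test assessments in school-based trials". The Discussion adds that "it might not be possible to retain the blinding of all research assistants at post-test assessments".

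**Primary outcome.** Under Functional capacity, "Students will be instructed to cover as much distance as possible in 6 min", and the distance in metres is recorded.

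**Exercise competence.** Under Physical literacy, "Competence will be assessed using video analysis of a selection of skills from the Resistance Training Skills Battery". The skills listed are push-ups, lunge, squat and front support chest touch. Under School-based HIIT sessions, the workouts include "foundational resistance exercises (ie, push up, squat, front support, and lunge". Intervention delivery says that phase 1 develops the foundational skills with technique cards.

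**The concern.** The commitment for the primary outcome is unconditional. The two acknowledgements are conditional but general, and the 6 min test falls within them. Someone who reads only the methods would take the primary outcome as assessed blind throughout. Someone who reads the whole article cannot tell what protection is intended.

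The 6 min test depends on effort and is given under an assessor's instruction, so an assessor who knows the allocation could influence it through encouragement. Competence is more exposed. It is a judgement of technique, the technique is what the programme teaches, and the written blinding commitment does not cover the people who score it. Followed as written, the plan allows unmasked rating of a taught skill. In both cases bias would most plausibly favour the intervention. Blinded analysis cannot undo bias that enters when a distance or a rating is recorded.

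**Working it through.** The plan gives no figure on blinding, so there is none to reproduce. The check is mainly a comparison of sections, followed by an illustration of what is at stake.

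**1. Which visits are at risk.** "Randomisation will occur within each cohort once consenting schools have completed baseline assessments". Baseline therefore precedes allocation and is safe. The risk falls on the follow-up visits, including the 6-month primary endpoint.

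**2. Do the statements agree?**

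| Place | Outcomes covered | Strength |
|---|---|---|
| Measures and data collection | primary only | unconditional, every time-point |
| Strengths and limitations | outcomes in general | may not be possible |
| Discussion | research assistants in general, at post-test | may not be retained |

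The Discussion speaks of retaining blinding. The only assessor blinding the article promises is for the primary outcome, so that statement most naturally includes it. The methods sentence carries no matching qualification.

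**3. Competence.** The scored and taught skills match: push-up, squat and lunge appear in both lists, and the front support chest touch corresponds to the front support. Because scoring is from video, it can be separated from the visit, so masking remains feasible even when the visiting team has learned the allocation.

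**4. Illustration of the stakes for the primary outcome.** Inputs from Sample size and power calculation: 30 schools, taken as k = 15 per arm; m = 7 students analysed per school; SD = 90 m; ICC = 0.2; baseline to post-test correlation r = 0.60.

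SE = √[2 × SD² × f × (1 + (m − 1) × ICC) / (k × m)]

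Here f depends on how baseline is used. The design effect is 1 + 6 × 0.2 = 2.2, and k × m = 105.

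- No baseline adjustment, f = 1: √(2 × 8100 × 2.2 / 105) = √339.4 = 18.4 m
- Change score, f = 2(1 − 0.60) = 0.80: √271.5 = 16.5 m
- Adjustment for baseline, f = 1 − 0.60² = 0.64: √217.2 = 14.7 m

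Suppose there is no true effect and assessors add an average of b metres to the group difference. The two-sided 5% error rate becomes 1 − Φ(1.96 − b/SE) + Φ(−1.96 − b/SE).

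| Assumed b | SE 18.4 m | SE 16.5 m | SE 14.7 m |
|---|---|---|---|
| 5 m | 5.8% | 6.1% | 6.3% |
| 10 m | 8.4% | 9.3% | 10.4% |
| 20 m | 19.2% | 22.9% | 27.4% |

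Every b is an assumption, and the documents support no particular value. Because b is an average over all assessments, it shrinks in proportion if only some assessors are unblinded. No comparable calculation is possible for competence, for which no variability is given.

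**The case against.** The strongest reply is that the authors have already disclosed the problem. The risk and its mechanism are in the strengths-and-limitations box, and the risk is repeated in the Discussion. Distance in metres is a fairly objective measure, and nothing describes how students are encouraged. Masking of video scorers, order of tests and a record of unblinding are operational details that a condensed article commonly leaves to the full protocol, which is available on request. That is fair: silence on them is not an error, and the measures proposed here are improvements. Disclosure does not settle the matter, however, because the methods sentence still promises what the limitations say may not hold, and its wording still stops at the primary outcome.

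A reader might infer more than the documents support:

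- **That the authors concede blinding will fail for the 6 min test.** Both acknowledgements say only that it might not be possible or retained, and neither names that test. It is an acknowledged risk.
- **That competence is scored unmasked.** The article does not say so. It does not commit to masking.
- **That the staff who help with questionnaires or film the skills also run the 6 min test.** The article does not say who films or scores, or whether these are the same people.
- **That masking is free, or that testing first guarantees blinding.** Coding clips takes work, and footage may carry cues to allocation. A teacher or student may reveal the allocation on arrival. An assessor who learns it at 6 months still knows it at 9 months.

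**Conclusion.** The point holds as an inconsistency and a gap in coverage that are cheap to close. The unconditional promise for the primary outcome does not fit the acknowledged risk at post-test, and the stated blinding omits a subjective, video-based rating of taught exercises for which masking is feasible.

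The size is unknown. The illustration shows only that an average bias of 10 to 20 m, small beside the 80 m target difference, would be enough to inflate the error rate to between about 8% and 27%. That rests on the assumed bias, on the planning values for SD, ICC and correlation, and on a normal approximation. The direction, towards the intervention, is a judgement that the documents do not establish. The point does not show that the primary result will be biased.

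**What to change.** 1. **Competence.** Extend the blinding statement to this outcome. Score coded clips, masked to arm and visit and in random order, using existing raters who did not visit the school concerned.
2. **Order of testing.** Run the 6 min walk/push test first at every visit, before questionnaires and skill filming. Include baseline so that the position of the test stays constant.
3. **Record of unblinding.** Have the assessor note, straight after the 6 min test, whether allocation had been revealed. Report the counts by arm as description only. Do not compare results by blinded status: disclosure happens after randomisation and is likely to differ by arm, because intervention students have a programme to mention, so the subgroups would no longer be randomised comparisons.
4. **Wording.** Reconcile Measures and data collection with the strengths-and-limitations box and the Discussion: state which outcomes have masked assessors, that blinding may be lost at post-test, and what is done about it. Softening the sentence to say blinding applies where possible would not be enough on its own, because it changes nothing the trial does.

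**Cost.** Clip coding, later competence scores, a less flexible visit order and one extra item on the assessment form. Running the 6 min test first may carry some fatigue into the sit-to-stand and push-up tests, but the order would be the same in both arms.
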